## Abstract

**Background:**

Adherence to prevention, care, and treatment recommendations among people living with HIV (PLHIV) is a critical challenge. Yet good clinical outcomes depend on consistent, high adherence to antiretroviral therapy (ART) regimens. Mobile phones offer a promising means to improve patient adherence and health outcomes. However, limited information exists on the impact that mobile phones for health (mHealth) programs have on ART adherence or the behavior change processes through which such interventions may improve patient health, particularly among ongoing clients enrolled in large public sector HIV service delivery programs and key populations such as men who have sex with men (MSM) and female sex workers (FSW).

**Objective:**

Our aim is to evaluate an mHealth intervention where text message reminders are used as supportive tools for health providers and as motivators and reminders for ART clients to adhere to treatment and remain linked to care in Ghana. Using an implementation science framework, we seek to: (1) evaluate mHealth intervention effects on patient adherence and health outcomes, (2) examine the delivery of the mHealth intervention for improving HIV care and treatment, and (3) assess the cost-effectiveness of the mHealth intervention.

**Methods:**

The 36-month study will use a facility cluster randomized controlled design (intervention vs standard of care) for evaluating the impact of mHealth on HIV care and treatment. Specifically, we will look at ART adherence, HIV viral load, retention in care, and condom use at 6 and 12-month follow-up. In addition, participant adoption and satisfaction with the program will be measured. This robust methodology will be complemented by qualitative interviews to obtain feedback on the motivational qualities of the program and benefits and challenges of delivery, especially for key populations. Cost-effectiveness will be assessed using incremental cost-effectiveness ratios, with health effects expressed in terms of viral load suppression and costs of resources used for the intervention.

**Results:**

This study and protocol was fully funded, but it was terminated prior to review from ethics boards and study implementation.

**Conclusions:**

This cluster-RCT would have provided insights into the health effects, motivational qualities, and cost-effectiveness of mHealth interventions for PLHIV in public sector settings. We are seeking funding from alternate sources to implement the trial.

## Introduction

### Background

Adherence to prevention, care, and treatment recommendations among people living with HIV (PLHIV) is a critical challenge facing HIV service delivery programs. Myriad personal, social, and systems level barriers influence adherence among PLHIV on antiretroviral therapy (ART). Difficulty managing treatment and forgetting to take medications or attend clinic appointments are common reasons for poor adherence [1-4]. Lack of social support, negative perceptions, poor communication with providers, and stigma and discrimination also may limit adherence [2,3]. In resource-poor settings, adherence challenges are amplified by structural and economic constraints such as residential dispersion that requires long travel times and has costs associated with travel and wage loss [3,4]. Key populations are disproportionately less likely to access and remain in care and treatment compared to the general population of PLHIV [5]. Good clinical outcomes depend on high adherence; consistent adherence to ART regimens is associated with reduced HIV RNA (viral load) levels, decreased transmission, higher CD4 cell counts, lower health care costs, and overall improved quality of life [6-9].

Mobile phones offer a promising means to improve patient adherence and health outcomes because they are private, portable, increasingly affordable, and nearly ubiquitous (88% use in Ghana [10]). Mobile phone interventions provide a means to address several of the key barriers to good adherence by providing reminders for care and a direct connection to health providers and facilities [11,12]. Research conducted in East Africa has shown that texting (short message service, SMS) reminders to ART clients’ mobile phones improved adherence and health [13-15]. Due to favorable findings from mobile phones for health (mHealth) interventions, limited proven adherence and treatment support interventions [3,16,17], and the need for a combination of interventions to address the complexities of adherence, mHealth programs are rapidly being scaled up globally [18,19].

### Justification for Study

Implementation research is needed to keep pace with mHealth program scale-up to provide guidance for optimal delivery and effectiveness of mHealth programs [3,18,20-22]. Although mobile phone reminders have been shown to improve medication adherence among new ART clients in a few health facilities, a trial conducted in one health facility in Cameroon with continuing ART clients did not improve adherence [21]. We have limited information about mHealth program effects on continuing ART clients and subpopulations in large-scale, public-sector HIV care and treatment programs where the majority of PLHIV in Ghana seek HIV care. Since women and key populations eg, female sex workers (FSW), and men who have sex with men (MSM), continue to be disproportionally affected by HIV, it is critical to assess effectiveness among these groups [3,5]. Moreover, the need for adherence support may be greater among continuing ART clients as opposed to new ART clients, as adherence challenges grow over time [23,24]. The support provided by mHealth interventions may influence ART clients’ adherence as well as retention in HIV care and treatment and adherence to other prevention and care directives such as use of condoms. Furthermore, there is little evidence about the motivational behavior change processes through which mHealth interventions improve patient health [25]. It is imperative to understand when, why, and how interventions work to develop a sound understanding of effectiveness to inform program scale-up [25,26]. Lastly, decision-makers and program implementers need mHealth cost-effectiveness data to guide resource allocation [14,27,28].

### Study Objectives

The main study goal is to evaluate the impact, implementation, and cost-effectiveness of a mobile phone adherence support intervention delivered to patients on ART in large-scale public sector health services in Ghana, especially for women and key populations. The study has three objectives: (1) to evaluate mHealth intervention effects on patient adherence and health outcomes; (2) to examine the delivery of the mHealth intervention for improving HIV care and treatment; and (3) to assess the cost-effectiveness of the mHealth intervention.

## Methods

### Study Design

This study is a two-arm, facility randomized, open, controlled trial. Of the public-sector health facilities in Ghana that provide ART to PLHIV in conjunction with the National AIDS Control Program (NACP)/Ghana Health Services (GHS), 40 will be randomly and equally allocated to receive either the mHealth intervention or standard of care. Approximately 1600 PLHIV who have been on ART for at least 6 months and who own a mobile phone will be enrolled. Data collection will occur at baseline and 6 and 12 months post-enrollment. A subsample of women and intervention participants from key populations including MSM and FSW, and health care providers and managers at intervention facilities, will be randomly selected to complete qualitative interviews at follow-up.

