#### Recruitment

Potential participants initially will be informed about the study by implementing partners at support groups and at the study clinics. In addition, peer educators who work with PLHIV will tell MSM and FSW about the study. Facility staff and clinicians also may apprise patients about the study. Interested PLHIV will be encouraged to speak with study staff at the facilities during predetermined study recruitment times; these times will be arranged during medication refill days or other times when substantive numbers of potential participants are likely to be in study facilities. Screening and enrollment will take place for interested volunteers in a private location in each health facility, where eligible participants will be enrolled until the target sample size is attained. Participants from intervention facilities will be enrolled into the mHealth intervention at enrollment. It is estimated that recruitment will take approximately 6 months to complete.

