### Sample Size

We calculated that a sample size of 40 clinics with 40 completed participants per clinic on average for a total of 1600 PLHIV is needed to detect a 15% improvement in adherence at 12 months, with 84% power and a (two-tailed) significance level of 0.05. These calculations assume that, at baseline, 65% of enrolled participants will be defined as having good ART adherence according to national guidelines (>90% adherent in Ghana). We have assumed approximately 20% participant attrition over the life of the study and have increased participant recruitment targets accordingly (N=2000). These calculations assume an intra-class correlation coefficient (ICC) of 0.05 due to the enrollment of participants and randomization by facility. The correlation (stability) in self-reported adherence over time that occurs within both clinics and subjects is assumed to be .50.

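### Study Design gives about 1600 as the number enrolled, but Sample Size needs 1600 completers and recruits 2000; the enrolment target should read 2000 throughout

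*Protocol article*

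**What the plan says.** Three sections of the protocol article bear on the number enrolled.

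- **Study Design**, describing who enters the trial: "Approximately 1600 PLHIV who have been on ART for at least 6 months and who own a mobile phone will be enrolled".
- **Sample Size**, on the number required: "a sample size of 40 clinics with 40 completed participants per clinic on average for a total of 1600 PLHIV is needed". On losses: "We have assumed approximately 20% participant attrition over the life of the study". The authors then say that they "have increased participant recruitment targets accordingly (N=2000").
- **Recruitment** (under Participants), on when enrolment ends: "eligible participants will be enrolled until the target sample size is attained". It gives no number.

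The power statement attached to the 1600 completers is that they suffice "to detect a 15% improvement in adherence at 12 months", "with 84% power and a (two-tailed) significance level of 0.05", given that "at baseline, 65% of enrolled participants will be defined as having good ART adherence".

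**The concern.** The same figure, 1600, is a count of people entering the study in one section and a count of people finishing it in another. The gap between the two enrolment figures is 400 people, a fifth of the recruitment target, which is too wide for the qualifier in Study Design to cover. That sentence describes eligibility and is followed by baseline data collection, so it cannot easily be read as meaning completers.

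The stopping rule under Recruitment does not settle the matter. Sample Size attaches the term sample size to 1600 and speaks of recruitment targets for 2000, so a site team could take the unnumbered target as either one. What depends on it is the total that sites work to, the recruitment plan of about 6 months, and whether the stated 84% power describes the trial that is run.

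**Working it through.** **1. The plan's own recruitment figure.** 40 clinics × 40 completers = 1600. Allowing for 20% attrition, 1600 / (1 − 0.20) = 2000. This matches Sample Size exactly, so the arithmetic there is right.

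**2. Completers if 1600 were enrolled.** 1600 × 0.80 = 1280, and 1280 / 40 = 32 per clinic on average.

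**3. Inputs for power.** From Sample Size: 65% good adherence, a 15% improvement, two-sided 0.05, ICC 0.05, correlation over time 0.50. From Study Design: 40 facilities allocated equally, so 20 per arm. From Primary Analyses: all models control for the baseline value of the outcome.

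**4. Formulas.** With m completers per clinic:
- design effect DE = 1 + (m − 1) × 0.05
- effective n per arm = 20m / (DE × f), where f = 1 − 0.5² = 0.75 with baseline adjustment and f = 1 without
- power = Φ(δ/SE − 1.96), with SE = √{[p₁(1 − p₁) + p₂(1 − p₂)] / effective n}

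The factor f is inferred from the stated correlation and the baseline-adjusted model. The protocol does not name a formula.

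**5. Reproducing the 84%.** At m = 40, DE = 2.95. Effective n per arm is 800 / 2.95 = 271 before the baseline factor and 271.2 / 0.75 = 361.6 after it. For 65% versus 75% (about a 15% relative gain), SE = √(0.415 / 361.6) = 0.0339, δ/SE = 2.95, and power = 83.9% (83.7% with pooled variance). This matches the stated 84%.

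**6. The same model with 1280 completers.** At m = 32, DE = 2.55. Effective n per arm is 640 / 2.55 = 251 before the factor and 334.6 after it. SE = √(0.415 / 334.6) = 0.0352, δ/SE = 2.84, and power = 81.0% (80.7% pooled). The loss is about 3 points. It is small because the number of clinics is fixed: 20% fewer participants reduces the effective sample only by 1 − 251/271.2, about 7.5%.

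**7. Range over other readings** (unpooled variance).

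| Reading | 1600 completers | 1280 completers |
|---|---|---|
| 65% vs 75%, f = 0.75 (reproduces 84%) | 83.9% | 81.0% |
| 65% vs 75%, f = 0.75, t with 38 df | 82.0% | 79.0% |
| 65% vs 74.75% (exact 15% relative), f = 0.75 | 82.0% | 78.9% |
| 65% vs 74.75%, f = 0.75, t with 38 df | 80.0% | 76.9% |
| 65% vs 75%, f = 1 | 72.5% | 69.1% |
| 65% vs 80% (absolute), f = 1 | 97.8% | 96.8% |
| 65% vs 80% (absolute), f = 0.75 | 99.6% | 99.3% |

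On the relative readings, the drop due to enrolling 1600 is about 3 points in every row. The absolute readings lose 1 point or less, but they give far more than 84% at 1600 completers and so do not reproduce the protocol's figure.

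**The case against.** The best defence is that the document comes close to settling this itself. Sample Size is the section that governs the number. It labels 1600 as completers, states the attrition, and gives 2000 as the only explicit recruitment target. Study Design is a hedged one-sentence overview, and the completer total was probably carried into it. Nothing in the calculation is wrong. This is largely right about what the authors probably meant, but no section says so, and the number missing from the Recruitment section is the one that would have made it plain.

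The second defence is that little power is at risk, and this stands. A reader might infer that the trial would be badly underpowered if 1600 were enrolled. The documents do not support that. On the reading that reproduces 84%, power stays above 80%. Figures just below 80% need a t reference or an effect of exactly 74.75%, neither of which Sample Size states. In those variants the full 1600 completers already give only 80 to 82%, which is a separate matter of how the 84% was obtained.

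A reader might also infer that enrolment is meant to stop at 40 per facility. Study Design gives no per-facility number, and the 40 per clinic in Sample Size is an average of completers.

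**Conclusion.** The inconsistency holds and does not depend on any power model: the enrolment figure in Study Design conflicts with the recruitment target in Sample Size, and Recruitment leaves its target unnumbered. It is a conflict of labels, and 2000 follows correctly from 1600 completers and 20% attrition.

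The consequence is conditional and modest. If enrolment stopped at 1600, about 1280 would complete and power would be about 81% instead of 84%. That size rests on attrition spread evenly across clinics, on a relative reading of the 15% (65% versus 75%), and on the 1 − r² factor. The last two are inferred because together they reproduce the stated 84%. If the 15% means absolute points, power would remain about 97 to 99% and the shortfall would have no practical effect, although that reading does not fit the protocol's own figure. The point deserves correction because an enrolment total should be unambiguous, but it does not undermine the design.

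**What to change.** In Study Design, state that about 2000 people living with HIV (about 50 per facility on average) will be enrolled, to yield about 1600 with 12-month data. Under Recruitment, define the enrolment target as N=2000 in total and refer to Sample Size. Do not turn the average of 50 into a fixed quota for each facility: Sample Size gives only an average, and facilities are stratified by number of ART patients.

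The cost is wording only. The 2000 is the protocol's own recruitment figure, so no participants are added to what Sample Size already plans. The article reports that the study was terminated before ethics review and implementation and that new funding is being sought, so the text can be corrected before it is used.

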### Facility Eligibility and Recruitment

The study will be implemented in health facilities in five regions of Ghana that have sufficient numbers of people on ART in public sector facilities and are accessible to study staff for data collection and monitoring. Specifically, eligible facilities must have at least 150 patients enrolled on ART, follow the national Ministry of Health guidelines for ART care and treatment [29], be a NACP/GHS facility, and they must not be extremely difficult to access due to very remote location or poor infrastructure for reaching the facility. To maximize facility homogeneity while balancing representativeness of clinics and participants, facilities meeting eligibility criteria will be stratified by geography (urban and rural) and number of ART patients receiving services. Facilities then will be recruited for study participation in proportion to their representation in the eligible facility population across strata until the target number of facilities is attained.

### Participants

#### Eligibility

To be in the study, participants must be between 18-49 years old, currently receiving ART at public sector facilities, enrolled in ART for a minimum of 6 months, and own a mobile phone. They also must live near the study facility and plan on residing near it for 12 months following study enrollment. Study volunteers who are currently participating in another HIV adherence study or who were involved in the mHealth pilot intervention will be excluded.

#### Recruitment

Potential participants initially will be informed about the study by implementing partners at support groups and at the study clinics. In addition, peer educators who work with PLHIV will tell MSM and FSW about the study. Facility staff and clinicians also may apprise patients about the study. Interested PLHIV will be encouraged to speak with study staff at the facilities during predetermined study recruitment times; these times will be arranged during medication refill days or other times when substantive numbers of potential participants are likely to be in study facilities. Screening and enrollment will take place for interested volunteers in a private location in each health facility, where eligible participants will be enrolled until the target sample size is attained. Participants from intervention facilities will be enrolled into the mHealth intervention at enrollment. It is estimated that recruitment will take approximately 6 months to complete.

#### Informed Consent

Participation will require written informed consent. Informed consent will be administered in English or Twi, the local language.

### Randomization

Once facilities are identified and agree to participate, they will be randomized within strata (urban/rural and number of ART patients) to the intervention or control group. Facility assignment will be revealed to field staff just prior to study initiation. Group assignment is needed before enrolling individuals and no blinding is possible. Eligible individual participants will receive the intervention or standard of care according to the assignment of the facility where they receive their HIV care and ART medication.

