### Analysis

#### Primary Analyses

Generalized estimating equations (GEE) will be applied to compare intervention and control arms on the key 6 and 12-month health outcomes. In order to adjust for variance in the outcomes at the facility-level, compound symmetric working correlation matrices will be used in all models. In order to maximize statistical power, all models will control for baseline measures of the outcomes. In addition, all models will include sex, stratification variables, and time on ART, as well as other covariates identified from the literature and to be specified in the final statistical analysis plan. Hypotheses will be tested at the 5% significance level for two-sided comparisons.

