### Limitations

There are a few study limitations worth noting. Supplementing routine data collection for ART clients with study-specific data collection reduces costs and participant burden; however, in collaboration with partners and facilities, great care will need to be taken to ensure high quality data, whether routine or study-specific, and across all time points. Self-reported adherence to ART has notable limitations, and we will complement self-reported data with objective measures from pharmacy, clinician, and laboratory data to provide a triangulated perspective on ART adherence. The health behavior constructs we will assess have rarely been evaluated in mobile phone interventions, but focus group data from LifeLine pilot participants suggests that the proposed constructs are impacted by mHealth programs. Finally, we will not be able to control external factors that may confound study results, such as medication supplies or health system challenges, civil or political influences, or other health or technology programs occurring in study communities during the intervention period, although we will document these contextual factors to help with interpretation of findings.

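### Facilities come from five regions but the randomisation does not balance region, so a region can by chance fall mostly in one arm; a constrained draw would prevent this cheaply.

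*Protocol article*

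**What the plan says.** The protocol article, under Facility Eligibility and Recruitment, states: "The study will be implemented in health facilities in five regions of Ghana". The same section says that "facilities meeting eligibility criteria will be stratified by geography (urban and rural) and number of ART patients receiving services", so geography there means urban or rural, not region.

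Under Study Design, "40 will be randomly and equally allocated to receive either the mHealth intervention or standard of care", which gives 20 facilities per arm. The Randomization section repeats the two sampling factors: after facilities are identified and agree, "they will be randomized within strata (urban/rural and number of ART patients) to the intervention or control group".

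Under Primary Analyses, "all models will include sex, stratification variables, and time on ART". Further covariates are left to the statistical analysis plan.

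The Limitations section says that "we will not be able to control external factors that may confound study results, such as medication supplies or health system challenges". It adds "other health or technology programs occurring in study communities during the intervention period" to the list and offers one response: "we will document these contextual factors to help with interpretation of findings".

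**The concern.** The protocol names outside influences that could distort the comparison and treats them as something that can only be recorded. Any of them that is shared across a region could be spread over the two arms by balancing region when facilities are allocated. All facilities, and so their regions, are known before the draw, but the draw uses only urban/rural location and number of ART patients.

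With 20 facilities per arm, uneven regional splits are common. If a stock-out or a competing programme then affected one such region during follow-up, part of its effect on adherence, refills or viral suppression would enter the arm difference, in either direction. Adjustment for the baseline outcome does not remove an influence that starts after baseline. The analysis plan can add region to a model, but it cannot change an allocation already drawn.

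**Working it through.** **Inputs from the protocol.** 40 facilities, 20 per arm; five regions; strata urban/rural and number of ART patients; 40 completers per facility; baseline good adherence 65%; intra-class correlation 0.05; correlation over time 0.50; two-sided 5% level; 84% power for a 15% improvement.

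**Assumptions, because the protocol gives no figures.** 8 facilities per region, with uneven sizes tried below; region unrelated to the two stratifiers; regional shocks of 5, 10 or 20 percentage points in adherence.

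**1. The planned effect.** The design effect is 1 + (40 − 1) × 0.05 = 2.95, so the effective size per arm is 800 / 2.95 = 271. Baseline adjustment multiplies the variance by 1 − 0.50² = 0.75.
- 15% read as relative and rounded, 65% to 75%: power 83.6%, which matches the stated 84%.
- 15% read as relative and exact, 65% to 74.75%: power 81.7%.
- 15% read as percentage points, 65% to 80%: power 97.6% without baseline adjustment and 99.5% with it.

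The yardstick is therefore about 10 points, with 15 points as the other reading of the text. For 65% against 75%, the standard error of the arm difference is √[(0.2275 + 0.1875) / 271] = 3.9 points, or 3.9 × √0.75 = 3.4 points with baseline adjustment.

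**2. How one region splits.** The number of a region's 8 facilities in the intervention arm is hypergeometric (40 facilities, 20 intervention, 8 drawn).
- 6:2 or worse: 2 × (0.0016 + 0.0202 + 0.0958) = 23.5%
- 7:1 or worse: 2 × (0.0016 + 0.0202) = 4.4%
- 8:0: 2 × 0.0016 = 0.3%

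**3. Any of the five regions.** Complete enumeration without strata gives 68.2% for at least one region at 6:2 or worse, and 18.7% for at least one at 7:1 or worse. Simulation with 4 or 6 strata gives about 68% and 19%, so the existing stratifiers barely change the result.

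For uneven regions, the chance that some region has at least 75% of its facilities in one arm is:

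| Assumed region sizes | Chance |
|---|---|
| 10, 10, 8, 6, 6 | 52% |
| 14, 10, 6, 6, 4 | 74% |
| 12, 10, 8, 6, 4 | 77% |
| 14, 10, 8, 4, 4 | 88% |

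The high figures come mostly from the 4-facility regions, which carry little weight. For a single region the chance is 60.5% with 4 facilities, 8.2% with 12 and 2.2% with 16.

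**4. Shift in the arm difference.** With a:b of a region's facilities in the two arms, a shock moves the difference by (a − b) / 20 of its size.

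| Shock | 6:2, factor 0.20 | 7:1, factor 0.30 |
|---|---|---|
| 5 points | 1 point | 1.5 points |
| 10 points | 2 points | 3 points |
| 20 points | 4 points | 6 points |

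**5. Set against ordinary sampling error.** Over all allocations the expected shift is zero. The standard deviation of the regional split is √[8 × 0.5 × 0.5 × 32/39] = 1.28 facilities, so the factor in step 4 has standard deviation 2 × 1.28 / 20 = 0.128. A 10-point shock in one region thus shifts the difference with a standard deviation of 1.3 points (2.6 for 20 points), against the planned standard error of 3.4 to 3.9.

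In variance terms, a 10-point shock in one fifth of facilities contributes 0.2 × 0.8 × 0.10² = 0.0016. The between-facility variance implied by the stated correlation is 0.05 × 0.65 × 0.35 = 0.0114, so the shock amounts to about 14% of it.

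**6. Room for a constrained draw.** With 8 facilities per region, about 1.2% of allocations already split every region 4:4. With four strata of 10 facilities (assumed) there are 252⁴, or about 4.0 billion, stratified allocations, so roughly 48 million remain acceptable.

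**The case against.** The strongest reply is that nothing in the protocol is wrong. Stratifying 40 facilities by urban/rural location and ART volume is a conventional choice. Facility randomisation makes the expected effect of a regional imbalance zero, and the intra-class correlation of 0.05 with facility-level GEE already allows for variation between facilities, including the part due to region. That stands: this is a loss of precision and of face validity, not a bias.

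A reader might infer that regional supply problems or programmes threaten the result and are likely to fall on one arm. The protocol does not support this. The Limitations section does not mention regions, and it places other programmes in study communities, which suggests a more local scale. A national stock-out would hit both arms whatever the split, and a shock at one facility would survive regional balancing. The 68% is also not the chance of harm. It is the chance that some region is uneven. Harm needs the affected region to be an uneven one (23.5% for a given region) and also needs a shock, whose probability is unknown.

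Nor can the absence of region from the listed covariates be counted as a fault, since others are left to the analysis plan.

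One part of the reply does not carry. The randomisation factors are fixed in the protocol, and the trial uses a single realised allocation that later adjustment repairs poorly when a region lies almost wholly in one arm.

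**Conclusion.** The point holds as a modest design weakness with a cheap remedy. Region is left to chance although it is known before the draw, and an uneven split of at least one region is more likely than not: about 68% with equal regions, and 52% to 88% over the uneven sizes tried.

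The effect on the trial is conditional. For a 6:2 split it is 1, 2 or 4 points for a regional shock of 5, 10 or 20 points, against about 10 planned (15 if the improvement is in percentage points). Averaged over allocations, a 10-point shock in one region adds error with a standard deviation of 1.3 points, well below the planned standard error. These figures rest on assumed region sizes, on region being unrelated to the stratifiers, and on shocks shared within a region. The validity of the test is not in question.

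**What to change.** - **Randomization.** Keep urban/rural and number of ART patients as strata. Draw the allocation by covariate-constrained randomisation, accepting only allocations in which each region's facilities split evenly to within one. Crossing five regions with the existing factors is not practical: even two size bands give 5 × 2 × 2 = 20 cells for 40 facilities.
- **Primary Analyses.** Include region as a covariate, because it then constrains the randomisation.
- **Limitations.** Say only that factors shared across a region are approximately balanced between arms by design, and that local factors remain uncontrolled and will be documented.

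The cost is one extra condition in a single computer-generated draw, with no added facilities or participants, and up to four facility-level model terms. The study was terminated before ethics approval and is seeking new funding, so the text can be changed before any allocation exists.
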